**PATIENTS**							
** *General information* **							
Demographics	Sex, age, education level, marital status	▲					
Medical data	Type of brain injury, date and time since injury, injury severity, lesion location	▲					
** *Social cognition* **							
Social Functioning Scale (SFS)	Functioning in social situations	●	● (daily)	● (twice a week)		● (twice a week)	●
Brock’s Adaptive Functioning Questionnaire – social scales (BAFQ-SOC) [41,42]	Social monitoring, empathy	▲			▲		▲
Dysexecutive Questionnaire – social scales (DEX) [43]	Metacognition, social convention, behavioral emotional self-regulation	▲			▲		▲
Interpersonal Reactivity Index (IRI) [44]	Cognitive and affective components of empathy	▲			▲		▲
La Trobe Communication Questionnaire (LCQ) [45]	Communication quality	▲			▲		▲
Cartoon test [46]	Mental state attribution	▲			▲		▲
Facial expression of emotion: stimuli and tests (FEEST) [47]	Facial affect recognition	▲			▲		▲
** *Neuropsychiatric symptoms* **							
Neuropsychiatric Problems Scale (NPS)	Severity of neuropsychiatric (behavior) problems, e.g., irritability, aggression, depression, anxiety	▲	▲ (daily)	▲ (twice a week)		▲ (twice a week)	▲
** *Partner relationship* **							
Relationship Quality Scale (RQS)	Perceived quality of relationship with significant other	▲	▲ (daily)	▲ (twice a week)		▲ (twice a week)	▲
Dutch Marital Satisfaction and Communication Questionnaire (DMSCQ) [48]	Marital satisfaction, negative communication and open communication	▲			▲		▲
** *Other cognitive measures* **							
Trail Making Test (TMT) [49]		▲					
Dutch version of the Rey Auditory Verbal Learning Test (15 Words Test) [50]		▲					
Zoo Mapping Test of the Behavioural Assessment of the Dysexecutive Syndrome (BADS) [43]		▲					
**SIGNIFICANT OTHERS**							
** *Social cognition* **							
Social Functioning Scale (SFS)	Functioning in social situations	●	● (daily)	● (twice a week)		● (twice a week)	●
Brock’s Adaptive Functioning Questionnaire – social scales (BAFQ-SOC) [41,42]	Social monitoring, empathy	▲			▲		▲
Dysexecutive Questionnaire – social scales DEX [43]	Metacognition, social convention, behavioral emotional self-regulation	▲			▲		▲
La Trobe Communication Questionnaire (LCQ) [45]	Communication quality	▲			▲		▲
** *Neuropsychiatric symptoms* **							
Neuropsychiatric Problems Scale (NPS)	Severity of neuropsychiatric (behavior) problems, e.g., irritability, aggression, depression, anxiety	▲	▲ (daily)	▲ (twice a week)		▲ (twice a week)	▲
Neuropsychiatric Inventory Questionnaire (NPI-Q) [51]	Neuropsychiatric symptoms	▲			▲		▲
** *Partner relationship* **							
Relationship Quality Scale (RQS)	Perceived quality of relationship with significant other	▲	▲ (daily)	▲ (twice a week)		▲ (twice a week)	▲
Dutch Marital Satisfaction and Communication Questionnaire (DMSCQ) [48]	Marital satisfaction, negative communication and open communication	▲			▲		▲
** *Other* **							
Caregiver Strain Index (CSI) [52]	Caregiver strain	▲			▲		▲

● = Primary Outcome Measure.

▲ = Secondary Outcome Measures.

**Fig 1 pone.0358008.g001:**
[figure not shown]
Participant timeline: Schedule of enrollment, interventions, and assessments.

SCED methodologies employ strategies designed to address concerns about internal validity. Key elements to consider in the design include randomization, blinding, and monitoring treatment adherence. The Risk of Bias in N-of-1 Trials (RoBiNT) Scale will be used to monitor and report the methodological rigor (i.e., internal and external validity) of the study design [40].

#### Randomization.

The multiple baseline design will be used to strengthen internal validity by controlling for threats such as history and maturation (i.e., in the case of brain injury spontaneous or natural recovery should be considered). Three different baseline lengths will be used: start treatment within 16–20 days, 21–27 days, or 28–33 days. This setup ensures that no participant waits longer than 4 weeks before starting T-ScEmo treatment, which aligns with the average waiting period for non-participating patients. The participants are randomly assigned to a baseline length by using a randomization tool. Randomization applies only to baseline length; all participants receive the intervention.

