**Methods and analysis:**

A non-concurrent, randomized, multiple-baseline single-case experimental design (SCED) will be employed to investigate the effectiveness of T-ScEmo in this study. At least 8 participants and a significant other will be randomly assigned to one of three baseline lengths. The primary outcome measures (social functioning, neuropsychiatric problems, relationship quality) will be assessed daily during baseline and twice a week during the treatment and maintenance phases. Secondary outcomes will be assessed at T0 (pre-treatment), T1 (post-treatment), and T2 (1-year follow-up). Both patients and the significant other will complete all outcome measures.

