### Sample size

We aim to include at least 8 patients and their significant others (i.e., 16 participants in total), with a maximum of 20 patients and their significant others (i.e., up to 40 participants). According to Tate et al. (2019) [56], a minimum of 3 participants is generally recommended to ensure sufficient variability and reliability of the data, as well as meet evidence standards. Moreover, replication across at least 3 participants is essential to draw robust conclusions. Given that the study design consists of 3 different baseline lengths – each considered a separate experiment in terms of the SCED design standards – it is ideal to include at least 3 participants per 3 baseline condition (i.e., a total of 9 participants) [56].

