#### Statistical analyses.

Statistical analyses of SCED data have gained prominence in recent years and will be used as a complementary method of data evaluation. There are still, however, no agreed-upon criteria for statistical analysis of SCED data [60]. Data from the frequently administered measures will be displayed and analyzed using the Shiny app for Single-Case Data Analysis [57]. The generated graphs will support visual analysis, and regression analysis will be conducted for quantitative assessment. Randomization tests (RTcombiP; [61]) will be applied to evaluate if levels of social cognition problems, social communication, social interaction, social problems, and neuropsychiatric problems differ significantly between phases (baseline versus treatment + follow-up).

If visually analysis yields strong or moderate evidence, effect size estimates will be calculated using non-overlap of all pairs (NAP) for the dependent variables: social cognition problems, social interaction, social communication, neuropsychiatric problems, and neuropsychiatric problems. To assess individual improvements on the periodic measurements (BAFQ, DEX, IRI, FEEST, Cartoon test, LCQ, DMSCQ, NPI-Q), the Reliable Change Index (RCI) will be calculated. The RCI will indicate whether post-treatment and follow-up changes are both statistically and clinically significant.

Reporting of the study will follow the Single-Case Reporting guideline In Behavioral interventions (SCRIBE) checklist [53], consisting of 26 items that outline the structure of a SCED report.

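### With three baseline lengths and the minimum of 8 patients, combining per-participant randomization p-values by a standard formula cannot give p < 0.05 for any effect size

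*Protocol article*

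**What the plan says.** The article's abstract says that participants "will be randomly assigned to one of three baseline lengths". The Randomization section gives the three lengths as day windows, "Three different baseline lengths will be used: start treatment within 16–20 days, 21–27 days, or 28–33 days", and adds that "The participants are randomly assigned to a baseline length by using a randomization tool" and "Randomization applies only to baseline length; all participants receive the intervention". No draw of a day within a window is described.

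Under Statistical analyses, "Randomization tests (RTcombiP; [61]) will be applied to evaluate if levels" of several outcomes differ significantly between baseline and the later phases. No alpha, test statistic or combination rule is given there.

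Under Sample size, "We aim to include at least 8 patients and their significant others (i.e., 16 participants in total), with a maximum of 20 patients". That number rests on a replication argument (three participants for each of three lengths, hence an ideal of 9), not on the properties of the test.

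**The concern.** A randomization test takes its p-value from the assignments that could have occurred. With three possible lengths per participant, the best individual result is rank 1 of 3. Standard formulas for combining p-values treat each one as continuous on 0 to 1, so they give little credit for eight results that could not have been better. The number of candidate starts, the minimum sample and the named test may therefore not fit together. If so, a trial that stops at its stated minimum would report a non-significant test even when every patient responded as strongly as the design can show, and a working treatment could be described as unproven.

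**Working it through.** **Inputs.** Candidate lengths per participant k = 3 (Randomization). Patients n = 8 minimum, 9 ideal, 20 maximum (Sample size). Assumptions, because the article is silent: alpha 0.05, the three lengths equally likely, and RTcombiP read as one test per participant with the p-values then combined. The article gives no power or minimum p-value, so there is no figure of its own to reproduce.

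**Step 1: individual floor.** The smallest p per participant is 1/k = 1/3.

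**Step 2: combined floor at n = 8, all eight at rank 1.**
- Additive rule: p = Σ_j (−1)^j C(n,j)(S − j)^n / n!, with S = 8/3. This gives (2557.1 − 476.3 + 1.1)/40320 = 0.0516.
- Stouffer: z for p = 1/3 is 0.4307; √8 × 0.4307 = 1.218, so p = 0.112.
- Fisher: 2 × 8 × ln 3 = 17.58 on 16 degrees of freedom, so p = 0.349.

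All three exceed 0.05.

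**Step 3: larger samples.**

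| n | Ranks | Additive p |
|---|---|---|
| 9 | all rank 1 | 0.0416 |
| 9 | one at rank 2 | 0.090 |
| 10 | all rank 1 | 0.0337 |
| 10 | one at rank 2 | 0.073 |
| 20 | all rank 1 | 0.0046 |
| 20 | three at rank 2 | 0.035 |
| 20 | four at rank 2 | 0.061 |

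With all at rank 1, Stouffer gives 0.098 at n = 9, 0.068 at n = 12 and 0.0425 at n = 16. Fisher gives 0.346 at n = 9 and 0.308 at n = 20.

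**Step 4: where the information is lost.** Under independent allocation there are 3^8 = 6561 joint assignments. The chance under the null that all eight have rank 1 is 1/6561 = 0.00015, yet the additive formula reports 0.0516 for that result. The combination formula causes the floor, not the randomization. With a balanced 3/3/2 allocation there are 8!/(3!·3!·2!) = 560 assignments, and the floor of a joint test is 1/560 = 0.0018.

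**Step 5: the day-level reading.** The windows hold 5 + 7 + 6 = 18 days. With 18 candidate starts, every rule falls below 0.001 at n = 8. That reference set is valid only if the day itself was drawn at random, and the article describes randomization only to a length.

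**Step 6: shape of the effect.** Candidate starts differ by at most 33 − 16 = 17 days, while treatment lasts 20 to 25 weeks. If a gain builds evenly over 20 weeks (140 days), at most 17/140 = 12% of it accrues within that span. Any randomization test on these lengths therefore responds mainly to change soon after treatment starts.

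**The case against.** The strongest reply is that the result depends on a chain of conditions: exactly 8 patients, alpha 0.05, three candidate starts and a continuous combination formula. Alpha and the rule are not stated, and how RTcombiP works rests on a cited source that is not at hand. Eight is a floor, 9 is called ideal, and the additive margin at 8 is only 0.0016. Details of this kind are commonly left to an analysis plan.

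Much of this stands as a limit on the wording. It does not remove the point. The number of lengths and the minimum of 8 are fixed in the article, the test is named there, and all three usual rules fail at that minimum. A ninth patient helps only under the additive rule, and only if all nine are at rank 1.

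A reader might infer three stronger things that the article does not support:
- **That the design can never yield a small p-value.** It can: a joint test over the same assignments reaches 0.00015.
- **That this is the only formal test of the repeated measures.** Statistical analyses also plans regression, calls statistics complementary to visual analysis, and makes the effect-size step depend on the visual grading rather than on this p-value.
- **That the day within a window is set by appointment scheduling.** The Blinding section says only that participants learn the start because appointments are made. How the day is chosen is not stated.

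No power percentage is offered here. One would need a standard deviation, an autocorrelation and an effect size that the article does not give. It would also have to follow the actual rating schedule, which is daily only in the baseline phase and twice weekly from the start of treatment.

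**Conclusion.** The point holds in conditional form. If RTcombiP combines per-participant p-values by the additive, Stouffer or Fisher rule and alpha is 0.05, the test cannot be significant at the stated minimum of 8 patients: the floors are 0.0516, 0.112 and 0.349. From 9 to 20 patients the additive rule becomes usable but tolerates few patients below rank 1, Stouffer is still above 0.05 at 12, and Fisher never gets below 0.30. The conclusion rests on three equally likely lengths and on reading the method from its name. It should be settled before analysis, because recruitment runs to the end of December 2026 and each patient's set of possible assignments is fixed at randomization.

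**What to change.** 1. Replace the combination of p-values by one pooled randomization test. The statistic is the mean phase difference over participants. The reference set is all joint assignments to the three lengths under the allocation scheme actually used (floor 1/6561 at n = 8, or 1/560 if balanced 3/3/2). State alpha.
2. Fix one rule for the start day that represents each window, and one rule for computing phase means. The second is needed because ratings change from daily to twice weekly at the actual start, so scores under the other assignments were not collected on the same days. Thinning daily ratings to twice weekly before taking means is one option.
3. Do not use an 18-day reference set unless the day was itself drawn at random.
4. Optionally, for new participants, let the randomization tool draw and record the exact start day within the existing windows. Each participant's reference set in the pooled test is then the list actually used for that participant, so earlier and later participants can be analyzed together.
5. State that the test is most sensitive to change soon after treatment starts and has low power for gradual change, so a non-significant result is not evidence of no effect.

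Cost: items 1, 2, 3 and 5 need revised analysis wording and a short script, with some care over item 2. Item 4 changes the randomization during recruitment, so it needs a documented amendment, one more draw per participant and appointments booked to match.

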#### Blinding.

Blinding participants and practitioners to phase is not feasible due to the behavioral nature of the intervention. Participants become aware of their baseline length after signing for study participation since they are told when the treatment starts (i.e., appointments are scheduled). The investigator is not blind since she coordinates and delivers the treatment. To reduce bias, the investigator will not visually or statistically analyze any data until data collection is complete. Additionally, neuropsychological assessments will be administered by trained staff (e.g., research assistants, interns or neuropsychologists) who are blinded to treatment phase through randomized scheduling. Participants complete digital questionnaires independently at home.

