#### Visual analyses.

As a first step, we will present the SCED data graphically and use visual inspection to determine whether differences between phases are apparent. The underlying assumption is that if differences are not visually apparent, they are unlikely to be statistically significant and clinically meaningful. Scores on frequently administered measures will be plotted graphically for each participant using the Shiny app for Single-Case Data Analysis (Shiny SCDA) in R [57,58] and analyzed visually. Intervention-related changes in outcome measures and the duration of change will be assessed based on the procedure described by Lane and Gast (2014) [59]. Visual analyses will focus on level, trend, variability, and overlap (i.e., extent of data overlap across phases). Evidence for a functional relationship will be categorized as follows: strong evidence (at least three demonstrations of the intervention effect and no demonstration of no effect), moderate evidence (at least three demonstrations of the intervention effect with at least one demonstration of no effect), and no evidence (fewer than three demonstrations of the intervention effect).

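### The stated protection for the unblinded, treating investigator's analysis is delay, which does not mask the visual reading that sets the evidence grade and opens the NAP calculation

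*Protocol article*

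**What the plan says.** The Blinding section of the protocol article accepts that participants and practitioners cannot be blinded to phase. Of the investigator it says: "The investigator is not blind since she coordinates and delivers the treatment". The next sentence gives the measure that covers her analysis: "To reduce bias, the investigator will not visually or statistically analyze any data until data collection is complete". The section's other blinding measure concerns the staff who administer the neuropsychological tests, "who are blinded to treatment phase through randomized scheduling".

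The Visual analyses section makes graphical inspection the first step. The team will plot the frequently administered scales for each participant and "use visual inspection to determine whether differences between phases are apparent". It lists what is read: "Visual analyses will focus on level, trend, variability, and overlap". The grade is then a count of demonstrations. The top category is "strong evidence (at least three demonstrations of the intervention effect and no demonstration of no effect", and the bottom one is "no evidence (fewer than three demonstrations of the intervention effect". Moderate evidence lies between: at least three demonstrations, with at least one of no effect.

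The Statistical analyses section calls the statistical methods complementary. It plans regression and randomization tests without making them conditional on the visual grade, but it does make the effect size conditional: "If visually analysis yields strong or moderate evidence, effect size estimates will be calculated using non-overlap of all pairs (NAP".

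**The concern.** A rule on when someone may analyse limits what she can do with the data while the trial is running. It does nothing about what she knows when she finally looks. By then the investigator has worked through treatment with her own patients, including the interim evaluation at session 11 and the treatment evaluation at session 20 (Table 3), and will have an impression of who improved.

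Visual inspection leaves more room for judgement than any other step in the analysis. If someone who knows the clinical course takes part in it, an ambiguous graph may be read in line with that impression. At stake are the headline evidence grade and the decision to report an effect size at all. The stated aim of reducing bias is met for study conduct, but not for this judgement.

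**Working it through.** No figure in the protocol depends on who reads the graphs, so there is nothing to reproduce. The check sets the sections side by side.

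1. **Who analyses.** The Blinding section regulates when the investigator may analyse visually and statistically. Such a rule makes sense only if she later takes part. The Visual analyses section says only that the team (we) will do it. Her participation is therefore a strong implication, not a statement.

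2. **What she knows.** She delivers treatment and is unblinded. The section on therapist training and adherence refers to neuropsychologists in the plural, and the Data analysis section lists the therapists involved as a characteristic to be described. Her knowledge of clinical course is certain only for the patients she treated.

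3. **What delay changes.** Before data collection ends, it prevents emerging results from influencing delivery, timing or follow-up. When the graphs are read, her knowledge of her own patients is the same with or without the delay.

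4. **Whether another measure covers the reading.** The blinded staff administer the face-to-face tests. The plotted series are the Social Functioning Scale (SFS) and the neuropsychiatric and relationship scales, which patients and significant others rate themselves. The coding described under Ethics and dissemination serves confidentiality; nothing says that it hides identity from whoever reads the graphs.

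5. **What depends on the reading.** On the SFS, which Table 1 marks as the only primary measure, there are 8 × 2 = 16 to 20 × 2 = 40 series (8 to 20 patients, two raters each). The grade has thresholds at small counts:
   - Moving from two demonstrations to three changes no evidence into moderate or strong evidence.
   - Where three demonstrations already exist, dropping a single no-effect reading changes moderate into strong.
   - Moving from no evidence to either higher grade also opens the NAP calculation.

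   Near a threshold, one reading is enough.

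6. **What does not depend on it.** The randomization tests and regression are planned regardless of the grade. They need no reading of a graph.

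To turn this into a number of misread series or a false-positive rate, one would need the share of ambiguous graphs and the rater's leniency. The protocol gives neither.

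**The case against.** The strongest reply is that the protocol never assigns the graph reading to the investigator, that an article may leave rater identity and coding to a fuller document, and that it does not claim that waiting blinds anyone. It discloses openly that she is not blind and commits to monitoring rigour with the RoBiNT Scale. The visual procedure is a published one with four named features and a preset counting rule, the randomization tests and regression run regardless, and de-identified data will be released so that others can re-read the series.

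Much of this stands, and it rules out several stronger readings that a reader might infer:

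- That the investigator alone judges every graph. The text implies her participation, no more.
- That she treated every participant through all 20 sessions. Several neuropsychologists may deliver treatment.
- That the study's whole conclusion hangs on the visual reading. The ungated statistical analyses are a real check.
- That a given number of series will be wrongly called effects. Any such count would rest on invented rates.

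The reply does not dispose of the point. The article chose to state a bias measure for this analysis, and the objection is to what that measure covers, not to a missing detail. The statistical methods are called complementary and do not alter the grade or the NAP condition. A preset counting rule does not mask the readings that are counted.

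**Conclusion.** The point holds in a limited form. The only protection stated for the unblinded investigator's visual and statistical analysis is delay, and delay does not address knowledge of clinical course when the graphs are read. That reading sets the evidence grade and the condition for calculating NAP.

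The conclusion rests on one inference, that she takes part in the reading, and applies to the patients she treated. If a non-treating reader is already planned, a sentence saying so settles that part. No numerical magnitude can be derived from the document; what can be said is that the grade can turn on one reading when the count is near three. The randomization tests and regression limit the harm without protecting the grade or the gate. The change is worth making because it is cheap and still possible: the Procedure section expects data collection to finish in April 2027, and no analysis by the investigator is to precede that.

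**What to change.** In the Blinding and Visual analyses sections, state that each graph is judged by an existing team member who treated none of the participants. The graphs should carry random codes, be shown in random order and omit patient and rater identity. The judgement should be recorded before the code is opened.

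If no such member exists, fix before data lock a computed rule for what counts as a demonstration, and keep the investigator's reading as descriptive. The rule could use level and overlap. It should not project the baseline trend forward: Table 1 gives 2 to 4 weeks of baseline against 20 to 25 weeks of treatment, so a trend would be carried over a phase 20/4 = 5 to 25/2 = 12.5 times as long, on a scale bounded at 1 and 10.

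In the Statistical analyses section, calculate NAP for every series whatever the visual grade. In the Blinding section, describe the waiting rule only as protection against data-guided conduct.

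The cost is a reassigned task or a short program, plus a few sentences; no new data or visits are needed. There are limits. The reader loses clinical context. Phase stays recognisable because ratings are daily in baseline and twice weekly afterwards, so the mask covers identity and clinical course, not phase. Bias in the ratings of unblinded patients and significant others is untouched.

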## Methods

### Study design

#### Phases and measurements.

A non-concurrent, randomized, multiple-baseline single-case experimental design (SCED) will be used in this study. In a SCED study, participants are repeatedly measured during all phases. The current study will be divided into four phases: baseline, treatment, maintenance, and follow-up. Repeated and frequent measures of the target behavior will be conducted within each phase. The rule of thumb is to collect data at least three, preferably five times per phase [38,39]. The primary outcome measure will be assessed daily during the baseline phase and twice a week in the treatment and maintenance phase. All secondary outcome measures will be assessed at T0 (baseline); a subset will also be assessed at T1 (post-treatment) and T2 (follow-up; 3–5 months post-treatment). See Table 1 and Fig 1 for an overview of the phases and measurements included in this study, including both primary and secondary outcome measurements.

**Table 1 pone.0358008.t001:** Overview of the phases and measures T-ScEmo4ALL Plus^+^.

Tests and questionnaires	Description	T0	Baseline (A)	Treatment (B)	T1	Maintenance (C)	Follow-up (D)/T2
Phase duration (weeks)			2 up to 4	20 up to 25		13 up to 21	

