### Procedure

Healthcare professionals at the Center of Excellence for Brain Injury and Neuropsychiatry who identify patients with an indication for treatment of social cognition problems will inform the researcher. Recruitment started on 1 January 2025. Participant recruitment is ongoing and will continue until the end of December 2026. Completion of data collection is anticipated in April 2027, and the study results are expected to be available by December 2027.

Psychologists will screen patients for eligibility based on the in- and exclusion criteria. Eligible patients will receive detailed information about the study. Then, patients will be invited to participate voluntarily during outpatient or clinical appointments. Those who consent to participate will be asked to sign an informed consent form. Upon providing informed consent, participants will be randomized to a baseline phase of varying duration, after which the T-ScEmo intervention starts, followed by maintenance and follow up phases.

Baseline measurements include a neuropsychological assessment, unless one has been conducted within six months prior to the start of the study. Furthermore, during this initial session, the therapist, together with the patient and the significant other, will formulate three treatment goals (TGA; Treatment Goal Attainment). Before, during, and after treatment participants complete multiple neuropsychological tests during a face-to-face appointment with a (trained) psychological assistant, intern or neuropsychologist. Participants and the significant other will complete a series of questionnaires digitally (see Table 1). They are free to choose when to complete the questionnaires and may pause and resume as needed.

In phases B and C, self-report scales are administered twice a week and must be completed before the next treatment session to ensure timely data collection. Post-treatment measurements will be conducted to evaluate the maintenance of treatment effects and to maintain consistency in the number of measurements across participants. A follow-up measurement will be conducted 3–5 months after treatment completion to evaluate long-term efficacy. Patients who choose not to participate will still receive T-ScEmo treatment, as it is considered standard care.

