### Primary outcome measure

*Satisfaction with social functioning* is assessed using a Social Functioning Scale (SFS), in which patients and significant others rate the patient’s functioning in social situations on a 10-point Likert scale ranging from 1 (“not at all”) to 10 (“entirely”). The item presented is: “How satisfied are you today with your (or your significant other’s) functioning in social situations?” To ensure a sufficient number of data points, as recommended for SCED studies, the SFS will be completed frequently: daily during phase A (2–4 weeks) and twice per week during phases B (20–25 weeks) and C (13–21 weeks). The SFS will be completed by both the patient and a significant other online (M-Path).

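### The stated mechanism, randomized scheduling, cannot blind test assessors to pre- versus post-treatment status, because only baseline length is randomized and the test visits are fixed around treatment

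*Protocol article*

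**What the plan says.** The Blinding section of the protocol article accepts that participants, practitioners and the investigator know the phase. It then claims one protection for the neuropsychological tests: they are administered by trained staff "who are blinded to treatment phase through randomized scheduling". The term randomized scheduling is not explained there or elsewhere in the article.

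The Randomization section gives the three baseline options ("start treatment within 16–20 days, 21–27 days, or 28–33 days") and says: "Randomization applies only to baseline length; all participants receive the intervention".

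The test visits are defined relative to treatment. The abstract states: "Secondary outcomes will be assessed at T0 (pre-treatment), T1 (post-treatment), and T2 (1-year follow-up"). The Phases and measurements section says that, after T0, "a subset will also be assessed at T1 (post-treatment) and T2 (follow-up; 3–5 months post-treatment"). The two passages disagree on the timing of T2, but both place it after treatment.

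Table 1 lists the FEEST and the Cartoon test at T0, T1 and T2. It lists the Trail Making Test, the 15 Words Test and the Zoo Mapping Test at T0 only.

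**The concern.** The FEEST and the Cartoon test are the only social-cognition measures in Table 1 that are not ratings by the patient or the significant other. Improvement on the FEEST is an explicit hypothesis under RQ1. Both tests also enter the Reliable Change Index analysis, which the Statistical analyses section says will show whether an individual's change is statistically and clinically significant.

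A tester who knows that a visit follows treatment may prompt, encourage or score differently. Any such shift goes straight into the change score. If the article's claim were carried into the results paper, readers would take these two outcomes as protected against that bias. The article also commits to monitoring and reporting rigor with the RoBiNT Scale, and the same claim could be carried into that report.

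**Working it through.** The article gives no figure to reproduce. The check is whether the randomized element could hide the phase of a test visit.

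**Inputs**
- Start of treatment: day 16 to day 33 (Randomization section).
- Treatment and maintenance lengths: "twice per week during phases B (20–25 weeks) and C (13–21 weeks") (Primary outcome measure section). In days, treatment is 20 × 7 = 140 to 25 × 7 = 175, and maintenance is 13 × 7 = 91 to 21 × 7 = 147.
- Assumption: T0 is at the start of baseline, counted as day 0.

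**Visit windows**
- Spread from randomization: 33 − 16 = 17 days at most.
- T1 earliest: 16 + 140 = day 156. T1 latest: 33 + 175 = day 208.
- T2 earliest: 156 + 91 = day 247. T2 latest: 208 + 147 = day 355. With the abstract's one-year follow-up it would be later still.

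The windows (day 0; days 156–208; days 247–355) do not overlap. If T0 could fall anywhere in baseline (days 0–33), the latest T0 would still come 156 − 33 = 123 days before the earliest T1 across patients. Within one patient the gap is at least the 140 days of treatment. Baseline randomization changes when treatment starts. It never changes which side of treatment a visit is on.

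**What the battery reveals**
- A session that includes Trail Making, 15 Words and Zoo Mapping is T0.
- A session without them is T1 or T2. Because every participant is treated, both are post-treatment.
- T1 and T2 contain the same tests (FEEST and Cartoon), so the battery does not separate those two visits.

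**Pre-study T0.** The Procedure section adds: "Baseline measurements include a neuropsychological assessment, unless one has been conducted within six months prior to the start of the study". An assessment done before enrolment cannot have been scheduled by any study randomization. For such a patient the test sessions that Table 1 leaves within the study, T1 and T2, are both post-treatment.

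**The case against.** The article does not define randomized scheduling or tie it to baseline length. The sentence in the Randomization section can be read as saying only that timing, not treatment, is allocated at random, which would leave room for random allocation of appointments among testers. Several types of staff are listed, and the article does not say who tests whom, so a tester need not have met the patient before. Figure 1 is not available here, and a fuller protocol may describe masking that a condensed article omits. The Procedure section also mentions testing during treatment, although Table 1 shows none.

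Part of this stands. A reader might infer that assessor blinding does not exist at all. The documents do not support that: testers could be masked by other means, and the article is merely silent on them. A reader might also infer that all three visits are identifiable. That is not shown, because T1 and T2 have the same test battery. Nor has any RoBiNT rating been given, so no rating can be called wrong.

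The core remains. Random allocation of testers to appointments would not remove the T0-only tests from the battery. Testing during treatment, if it happened, would not put the visits in random order. The concern is not a missing detail: the article makes a positive claim and names a mechanism that cannot deliver it.

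**Conclusion.** The concern holds in this limited form: randomized scheduling, as the article describes the design, cannot mask pre- versus post-treatment status from the testers. It is a wrong statement about bias control and should be corrected.

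Its reach is the FEEST, the Cartoon test and their Reliable Change Index results, all secondary. The primary Social Functioning Scale is completed online by the patient and the significant other and is untouched. The direction and size of any bias cannot be estimated from the document.

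The conclusion assumes that Table 1 shows the full test schedule and that no other masking procedure is in use. If one is, the remedy is to describe it.

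**What to change.** 1. Withdraw the phrase on randomized scheduling, or replace it with a masking procedure that can work and is described.
2. Do not report the FEEST and Cartoon results as phase-blinded on the strength of randomized scheduling, in the results paper or in the RoBiNT report.
3. As a partial safeguard, add masked re-scoring for the outcome analysis. After data collection, staff of the types already listed who did not test that patient would re-score the FEEST and Cartoon records in random order, with visit labels and dates removed.

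The T0 scoring must stay as it is, because test results bear on eligibility (Table 2) and are explained to the patient and significant other in Session 1 (Table 3). Step 3 is therefore a second scoring, not a postponed one.

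**Cost:** a change of wording, a less favourable statement about bias, and some duplicate scoring. Re-scoring protects the scoring only; it does nothing about tester influence during the face-to-face session. Its value also depends on how much judgement the scoring involves, which the article does not say. The Procedure section plans recruitment to the end of December 2026 and completion of data collection in April 2027, and re-scoring comes after that, so it can still be arranged.
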